### Plans to promote participant retention and complete follow-up

PR-staff retention will be promoted at each site by having a designated link researcher from the IMPROVE team. These researchers will attend 2 out of the 3 days of PR-buddy training to assist with completion of trial-related paperwork, such as consenting PR buddies and completion of volunteer agreements. The link researcher will visit intervention sites monthly to collect recorded phone data and to link with the PR team regarding any other research management issues.

PR buddies will attend monthly meetings at which they will be offered ongoing support from PR staff. The support will include checking on interactions with patient participants, identifying any patient participants who the PR buddy is having difficulty supporting and providing remedies, sharing experience and solutions to common problems. PR buddies who withdraw while they are supporting patients will be asked to stay in contact with these patients until they end of their PR. If they are not able to do this, then the patients will be reassigned to another PR buddy by PR staff. Patient participants who wish to withdraw will be invited to complete the follow-up data collection questionnaires before leaving the trial.

Any PR staff or PR buddies who choose not to or are unable to continue until the end of the trial will be asked to participate in a qualitative interview as part of the process evaluation. Data that are collected before patient participants withdraw will be retained for analysis.

### Data management

Quantitative data will be stored electronically on a secure bespoke trial database provided by King’s Clinical Trials Unit (KCTU). Paper data will be kept in locked filing cabinets in secure rooms accessed with staff passes at either King’s College London (KCL), the University of Leeds or in the site file at PR sites. Participant contact details will be stored in a locked filing cabinet, or on a secure university computer server.

All mobile phones lent to PR buddies will be passcode protected. IMPROVE research staff visiting sites will use encrypted laptop computers to download recordings from phones lent to the PR buddies which will be kept in a locked filing cabinet when on the university sites. Audio-recorded data will be uploaded to access-restricted servers at KCL and then deleted from the phones.

Data from PR services, such as PR attendance, will be transferred using secure NHS email.

A 10% sample of data entered into the electronic database will be checked every 3 months against source data. Data management will be audited every 12 months.

Personal information held by the research team will include necessary information for telephone and mail contact including address and telephone number. Demographic and outcome data will be anonymized before entry into a database. A participant identification key will be held in encrypted files separate from the database. All publicly available data will have been anonymized.

No laboratory samples will be used in this trial.

### Statistical methods for primary and secondary outcomes

Except for enrolled clusters/patients who are found to be ineligible or who withdraw consent at baseline visit and so never receive any treatment, and for whom no data are available, main analyses will be on an intention to treat basis to reflect the randomisation process.

Chi square test adjusting for cluster effect will be used to compare the rates of completion of PR in the two trial arms. Further, a mixed effect logistic model will be used in a sensitivity analysis to adjust for potential confounders, including age, gender and site size. In addition, adjustment for cluster-level variables will be applied for selected variables including site (cluster) size.

The estimates for primary outcome will be presented as odds ratios with 95% confidence intervals for the effect of intervention. Statistical significance will be determined at 5% level using a two-sided test throughout.

A generalised linear mixed model with linear link function will be used to analyse secondary continuous outcome measures. Working correlation matrices will be unstructured, which is not unduly restrictive given that measurements are only taken at three time points. The sandwich estimator of covariance matrix will be used to obtain appropriate (consistent) estimates of precision. Analysis of secondary endpoints will be done at the individual level.

The study has no interim analysis planned.

### Methods for additional analyses

Subgroup analyses of the principal outcome measure, completion of pulmonary rehabilitation, are planned to assess the impact of the following: the number of pulmonary rehabilitation sessions attended by patient participants; interval between offer of appointment for pre-PR assessment and first PR class; type of pulmonary rehabilitation programme (rolling or cohort).

Multiple imputation methods will be used, incorporating any available information from the baseline assessment and explanatory variables to impute missing primary or secondary outcome measures. Sensitivity analyses to assess the robustness of the results to various assumptions regarding missing data, or participants lost to follow-up, will be conducted.

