## Introduction

### Background and rationale

Chronic obstructive pulmonary disease (COPD) is the most common chronic lung disease caused by smoking [1]. More than a million people in the United Kingdom (UK) live with the condition, with a higher prevalence typically reported in more deprived areas [2, 3]. The symptoms of COPD include cough, breathlessness and fatigue [4]. A severe exacerbation of COPD symptoms is a key cause of attendances at Accident and Emergency departments and of hospital admissions in the UK [5]. COPD is also the third most common cause of death in England and Wales [6].

The most effective treatment for the symptoms and disability associated with COPD is pulmonary rehabilitation (PR) [7]. PR is a prescribed exercise-based treatment programme which has been identified by NICE (The National Institute for Health and Care Excellence) as one of the “five fundamentals of COPD care” [8, 9]. Structured group classes include physical exercise and information on self-management. Social interaction is a notable element in almost all services. The effectiveness of PR in improving symptoms, quality of life and exercise capacity in people living with COPD has been demonstrated conclusively in a longstanding Cochrane review now close [10]. More recently, PR has also been associated with improved survival following discharge from hospital after a COPD exacerbation [11].

Despite strong evidence demonstrating the effectiveness of PR, patients likely to benefit from it often do not receive a referral by healthcare professionals or do not join the programme. In an audit of PR services in England and Wales in 2015, the annual number of referrals of patients with COPD to 240 services was estimated to be 68,000 [12]. This equated to approximately 5% of the estimated 1.3 million people with symptomatic COPD. If patients were referred every 5 years (annual referral is desirable), the rate of referral of appropriate people with COPD would be still only 25%. In subsequent audits, 62% of the eligible patients who were referred to PR joined the programme, and 65% of those who joined the programme completed PR, an overall rate of uptake and completion of 40% [12]. The American Thoracic Society and European Respiratory Society have recommended a more collaborative approach between clinicians, patients, and funders to improve the delivery of PR within healthcare services [13].

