### Objectives

The primary objective of the IMPROVE trial is to assess the effectiveness of the intervention using volunteer PR buddies trained by PR teams to improve completion of PR in patients with COPD. The working hypothesis for the trial is that PR experienced volunteer PR buddies, recruited and trained by PR staff to support COPD patients newly referred to PR, will improve uptake and completion of PR in comparison with usual care.

The secondary objectives include:To assess the intervention fidelity with respect to:The training of PR teams to set up and run a PR-buddy serviceThe recruitment and training of PR buddies by the PR teamsThe delivery of the support intervention to patients by the PR buddiesTo assess the acceptability of the intervention to trial participants, including PR staff, PR buddies and patient participants.To identify PR service, PR-buddy and patient-participant factors associated with the implementation, delivery and impact of the intervention.To conduct within-trial and longer-term cost-effectiveness analyses of the intervention compared to standard care.

The trial includes an internal pilot being conducted in eight sites, four in the intervention arm and four in the control arm. The aims of the pilot are:Testing of the PR staff training (intervention sites)Testing the feasibility of PR teams recruiting and training a group of PR buddies (intervention sites)Implementation of a PR-buddy support service to COPD patients referred for PR (intervention sites)Recruitment of patient participants (all sites)

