### Outcomes

The primary outcome is completion of PR by each individual patient participant, summarised as a proportion for each trial site. Standard PR treatment usually consists of a pre-PR assessment, twelve classes over 6 to 8 weeks and a final assessment. Uptake is defined as attendance at the pre-PR assessment; completion is defined as attendance of 75% or more of the planned PR sessions—usually at least 9 out of 12 sessions [31, 32].

The secondary outcomes are:The proportions of PR sites that were recruited and that were retained—measured through a site recruitment log and a record of withdrawal/default.Demographic and clinical characteristics of PR buddies in participating sites measured through data collected and recorded on the PR-buddy application form.The proportions of patient participants that were recruited and retained—measured through a site log rate of acceptance of the invitation to participate, rate of assessment for PR and rate of participants followed through to completion.Demographic and clinical characteristics of patient participants in participating sites measured through data collected and recorded on Case Report Forms (CRFs) at recruitment and consent interview.Exercise capacity being assessed at the pre-PR assessment, respiratory-specific quality of life and psychological wellbeing measured at baseline, at 3 months and at 6 months in a questionnaire. Exercise capacity will be measured through site records of the 6-min walking distance test or the incremental shuttle walk test or the 60-s sit to stand test [33–35]. Quality of life and psychological wellbeing will be measured by the Chronic Obstructive Pulmonary Disease Assessment Test and the Hospital Anxiety and Depression Scale in a postal questionnaire [36, 37]. Breathlessness will be measured by the Medical Research Council breathlessness questionnaire [38].

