### Recruitment

At time of writing (October 2023), site recruitment is underway. The trial is being promoted in PR services across England and Wales through emails, phone calls, presentations at regional PR-network meetings, meetings with local Clinical Research Networks and conferences. Services interested in becoming a trial site are asked to complete an expression of interest form. PR staff in eligible sites are invited to an information meeting. The expression of interest form and information meeting are used to ascertain if the PR service meets the site eligibility criteria. The IMPROVE trial manager liaises with the local NHS research and development department in relation to assessment of capacity and capability and to get a site agreement in place. A site initiation visit will be held then. The site will be randomised then. All sites will nominate a site Principal Investigator to take overall responsibility for the leadership and conduct of the research at their site.

In sites randomised to the intervention PR staff nominated to undertake the PR-staff training will be consented as trial participants by IMPROVE research staff. Eligible PR buddies will be recruited by the trained PR staff, who will write to COPD patients who have completed PR in their service within the last year. All interested respondents will be screened for eligibility in a phone call. Those considered eligible will then be invited to interview. All those who successfully complete the interview will be invited to attend the PR-buddy training at that site. Consent will be obtained from PR buddies at the first training day.

Patient participants referred for PR will be informed about the trial at the time they are offered a pre-PR assessment appointment. Recruitment and consent of patient participants will be completed by local NHS research delivery staff or local Clinical Research Network staff who are blinded to the outcome of randomisation for the PR service.

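### Subgrouping completion by sessions attended is circular, and subgrouping it by interval to first class is open to selection bias

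*Protocol article*

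**What the plan says.** The section Methods for additional analyses states: "Subgroup analyses of the principal outcome measure, completion of pulmonary rehabilitation, are planned to assess the impact of the following". Three factors follow. The first two are "the number of pulmonary rehabilitation sessions attended by patient participants; interval between offer of appointment for pre-PR assessment and first PR class"; the third is programme type, rolling or cohort.

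The Outcomes section gives the definitions on which this turns: "completion is defined as attendance of 75% or more of the planned PR sessions—usually at least 9 out of 12 sessions", and "Uptake is defined as attendance at the pre-PR assessment".

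Under Recruitment, sites are randomised around site initiation, and patients come in afterwards: "Patient participants referred for PR will be informed about the trial at the time they are offered a pre-PR assessment appointment". The Objectives give the hypothesis that PR buddies "will improve uptake and completion of PR in comparison with usual care", so uptake is itself a target of the intervention. The Background cites audit figures: "62% of the eligible patients who were referred to PR joined the programme, and 65% of those who joined the programme completed PR".

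The statistical methods section makes a cluster-adjusted chi-square test the primary comparison, uses a mixed-effects logistic model as a sensitivity analysis, and reports the primary outcome as an odds ratio. Programme type is a minimisation factor in the main trial.

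**The concern.** A subgroup analysis asks whether the treatment effect differs between groups of patients or sites that were fixed before treatment could act. Two of the three factors do not meet that condition.

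Sessions attended is the variable that is cut to form the outcome. Stratifying completion by it conditions on the outcome.

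The interval to the first class is observed after allocation, can be lengthened or shortened by buddy support, and on its natural reading is recorded only for those who reach a class. Comparing arms within interval bands then compares two groups of starters that the intervention may have selected differently.

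At stake is the reading of two prespecified analyses of the primary outcome. One cannot return a treatment effect. The other could show no effect, or an inflated one, while the effect in all participants stays the same, and be taken for effect modification.

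**Working it through.** **1. The plan's own figures.** From the Background: 0.62 × 0.65 = 0.403, the stated 40%. From the Sample size section: 0.40 × 1.40 = 0.56. The overall odds ratio for 40% v 56% is (0.56/0.44) / (0.40/0.60) = 1.91. The stated site number also reproduces. The pooled two-proportion formula (two-sided 5%, 90% power, no continuity correction) gives 203 per arm. The design effect is 1 + 29 × 0.056 = 2.624, and 203 × 2.624 / 30 = 17.8, so 18 sites per arm. Nothing below alters it.

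**2. Sessions attended.** With 12 planned sessions the threshold is 0.75 × 12 = 9.

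| Sessions attended | Completion, control | Completion, intervention |
|---|---|---|
| 0 | 0% | 0% |
| 1–4 | 0% | 0% |
| 5–8 | 0% | 0% |
| 9–12 | 100% | 100% |

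The risk difference is 0 in every row and the odds ratio cannot be estimated, whatever the overall effect. A band that straddles 9 would mix completers and non-completers, but it would still select patients on part of the outcome.

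The article says only that 12 sessions are usual. If the planned number varied from 8 to 16 (assumed), the threshold would run from 6 to 12. A raw count pooled over sites would then not be perfectly deterministic, but the same table holds within each programme.

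**3. Who has an interval.** At 62% uptake, 1 − 0.62 = 38% of controls have no first class, and all of them are non-completers. Uptake is defined as attending the assessment. If the audit figure follows that definition, the share without an interval is at least 38%, because some assessed patients may never attend a class. The planned multiple imputation covers outcome measures and cannot supply an interval that never occurred.

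**4. Effect among starters.** Write completion as uptake × completion among starters. Control is 0.62 × 0.65. Take intervention completion as 0.56 and vary how it is reached; the article does not give the split, so this is an assumption.

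| Route of the gain | Uptake, intervention | Completion among starters, intervention (control 65%) | Odds ratio among starters |
|---|---|---|---|
| Uptake only | 0.56/0.65 = 0.862 | 0.650 | 1.00 |
| Equal factors, √(0.56/0.403) = 1.179 each | 0.731 | 0.766 | 1.76 |
| Retention only | 0.620 | 0.56/0.62 = 0.903 | 5.03 |

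For example, the last row is (0.903/0.097) / (0.65/0.35) = 5.03, computed before rounding. The overall odds ratio is 1.91 in every row (1.89 if control is taken as 40.3% rather than 40%). The share of the intervention arm without an interval runs from 14% (uptake only) to 38% (retention only).

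**5. Sign reversal.** Suppose patients who start only because of a buddy complete less often than others (assumed 20% to 40%), and uptake rises to 75% or 86% (assumed). Completion among starters is [0.403 + (u − 0.62) × c] / u, where u is uptake and c is completion in the added starters. With u = 0.75 and c = 0.40 this is 0.455/0.75 = 0.607, 4 points below control, while overall completion rises by 0.455 − 0.403 = 5 points. With u = 0.86 and c = 0.20 it is 0.451/0.86 = 0.524, 13 points below control, while overall completion rises by 5 points.

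**The case against.** The strongest defence concerns the interval. It does not determine completion, which still varies among patients who start, and an association among starters can be described and interpreted. One secondary objective is to identify service and patient factors associated with the intervention's impact, and the wording of the subgroup plan could be read in that spirit. The article also does not say whether the first class is the scheduled or the attended one, whether the interval is a patient or a site value, or how patients without one are classified; such detail commonly sits in an analysis plan that is not shown. All of this stands. A reader might infer that both subgroup results are meaningless, and the documents do not support that for the interval. Its defect is selection bias in a between-arm comparison.

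A reader might also infer that the interval analysis would hide the whole effect, because completion among starters would be 65% in both arms. That is one end of the range above and requires the entire gain to come through uptake. The Objectives name uptake and completion together, so patients who start and may drop out are targets too.

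None of this rescues the sessions factor. The article itself names the factor and defines the outcome by it, so later detail would have to contradict the text. Reading it as plain association does not help either: sessions predict completion because they define it.

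**Conclusion.** The concern holds in two parts of different strength. The analysis by sessions attended cannot work: within any one programme, completion is 0% or 100% in both arms on either side of the threshold. This follows from the definition and needs no assumption beyond the usual 12 sessions for the worked table. The analysis by interval is prone to selection bias. On the natural reading it leaves out about 38% of controls, and the odds ratio among starters could be anywhere from 1.00 to 5.03 for the same overall 1.91. That range rests on the audit figures applying to trial controls, on treating those who joined as having an interval, and on an assumed split between uptake and retention.

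A reader might take this as a flaw in the trial's main result. It is not: the main comparison is by intention to treat, and the sample size does not depend on these analyses. Programme type is a sound factor. The point should be fixed, but it does not threaten the primary conclusion.

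**What to change.** - Drop sessions attended as a subgroup factor. Report it by arm as an outcome in all participants, with non-starters counted as 0.
- Either label the interval analysis as an exploratory, non-randomised association among starters, or replace it with a site-level value that relates to the period before randomisation. The look-back uptake and completion proportions in Data collection and management are candidates. They are requested once a site has its green light, and the order relative to randomisation is not stated, so confirm the timing first. That section lists no waiting-time measure, so these would replace the interval as a modifier, not measure it.
- Keep programme type and test it as an arm-by-type interaction in the mixed-effects logistic model. The chi-square primary test has no place for an interaction.

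The cost is wording in the protocol and analysis plan. On the first and third changes no new data are needed; the second needs only a check of dates if the site-level option is chosen.

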### Health economic analysis

We will conduct within-trial cost-effectiveness and cost-utility analyses for the 6-month period after patient recruitment, which will be extended to 1, 3 and 5 years by a decision model if the intervention is effective at increasing PR completion. These economic evaluations will adopt the viewpoints of NHS and personal social services as well as that of society and be developed based on guidance for good practice, and decision support for NICE [40, 41].

Costs will encompass resources required to set up the intervention (e.g. training and recruitment of PR staff and PR buddies) and intervention delivery (e.g. ongoing meetings / support of PR staff and PR buddies, travel by PR buddies). Patient-level costs collected will cover meetings attended and resource use consequences for primary and secondary care, and personal social services, as well as out-of-pocket expenses (e.g. travel) borne by patients. Provider costs will be valued using national unit prices where possible to facilitate generalisability followed by published literature or if unavailable, local costs [42, 43]. Patient time will be valued using average income by age [44].

Outcomes for economic evaluation will be measured in natural units for cost-effectiveness analysis (e.g. cost per % change in completion rate, cost per % change in uptake rate). Quality-adjusted life years (QALYs) for cost-utility analysis will be measured with the EQ-5D-5L and calculated using the under the curve method with utility values taken from the UK social tariff [45, 46].

The analyses will present the incremental cost-effectiveness ratios, cost-effectiveness acceptability curves and incremental net benefit, based on willingness-to-pay thresholds of British pound sterling (GBP) 20,000–30,000 per QALY gained. Deterministic and probabilistic sensitivity analyses will examine whether the findings are sensitive to alternative approaches in handling missing data, or patient subgroups based on their completion of PR, and to examine the uncertainty in the assumptions on disease progression or service use beyond trial period and the range of the input data.

